## Abstract

**Introduction:**

Many people quit smoking during pregnancy, but postpartum smoking relapse is common. Maintaining smoking abstinence achieved during pregnancy is key to improving maternal and child health. There are no evidence-based interventions for preventing postpartum smoking relapse. This trial aims to determine whether an intervention to prevent postpartum relapse is effective and cost-effective.

**Methods and analysis:**

A randomised controlled trial of a complex intervention to prevent postpartum smoking relapse (BabyBreathe), with internal pilot, economic and process evaluations. Participants are adults who are pregnant and who report having quit smoking in the 12 months before, or during pregnancy. Participants are eligible if they read and understand English, and provide informed consent. Following consent and biochemical validation of smoking abstinence, participants are randomised to intervention or usual care/control (no specific relapse prevention support). The BabyBreathe intervention consists of manualised advice from a trained member of the health visiting service, health information leaflets for participants and partners, access to the BabyBreathe website and app. At the time of birth, participants are posted the BabyBreathe box and support is provided by text message for up to 12 months postpartum. Target sample size is 880, recruiting across midwifery services at four hubs in England and Scotland and through remote advertising in England, Scotland, Wales and Northern Ireland. Outcomes are collected at 6 and 12 months. The primary outcome is self-reported sustained smoking abstinence at 12 months, carbon monoxide verified. Secondary outcomes include self-reported abstinence, time to relapse, partner smoking status and quality of life.

**Ethics and dissemination:**

The trial was approved by the North West Preston Research Ethics committee (21/NW/0017). Dissemination will include publication in peer-reviewed journals, presentation at academic and public conferences including patient and public involvement and to policymakers and practitioners.

**Trial registration number:**

ISRCTN70307341

Strengths and limitations of this studyThis is the largest international trial of a postpartum smoking relapse prevention intervention, specifically developed to support sustained postpartum smoking abstinence.The intervention (BabyBreathe) is theory based, drawing on behaviour change techniques, systematic reviews of existing evidence and extensive patient and public involvement.An embedded mixed-methods process evaluation will assess implementation, mechanisms of impact and contextual influences, as well as acceptability and which elements of the intervention are perceived to be most effective, for which women, in which circumstances.The study is resource intensive and is limited by the capacity of clinical services. The trial protocol allows flexible options for recruitment and intervention delivery to support clinical teams in delivering the intervention.The trial is recruiting across the UK and includes a cost-effectiveness evaluation.

## Introduction

Around a quarter of UK women report smoking in the year before pregnancy.^1–3^ More women quit smoking during pregnancy than at any other time, with as many as 45% able to ‘spontaneously quit’.^4^ However, there are marked health inequalities, as younger mothers and women with lower income are both less likely to quit and more likely to relapse.^5 6^ There is a unique opportunity to help women who cease smoking in pregnancy to quit permanently. Most women who quit smoking wish to remain abstinent after the birth; however, up to three-quarters of spontaneous quitters return to smoking within 6 months.^7^ Postpartum relapse is a major public health problem; yet there are no evidence-based interventions, and no routine support is offered to prevent relapse.^8^ The National Health Service (NHS) Long Term Plan prioritises smoking cessation services in pregnancy,^9^ overlooking postpartum support. Supporting sustained abstinence may be critical to reaching the UK government ‘smokefree 2030’ target.^10^ This trial will build on the success of cessation interventions in pregnancy,^11^ by trialling a theory-based relapse prevention intervention developed by our team.^12^

Previous interventions to support sustained smoking abstinence post partum consist of brief and skills-based education, but when pooled, studies overall did not demonstrate effectiveness.^13^ A recent Cochrane review of relapse prevention interventions included postpartum relapse prevention trials as a subgroup. Fifteen studies included postpartum follow-up but there was no significant benefit of interventions.^8^ New approaches are urgently needed to address this global public health issue. The recent Cochrane review concludes that: ‘Future studies may be better advised to focus on alternative approaches not studied extensively or at all so far, such as opportunistic use of nicotine replacement, contingency management, social support, cue exposure (only imaginary exposure has been studied so far), interventions aimed at maintaining abstainers’ morale and awareness of the danger of slips, and so forth’.^8^ Sustained postpartum smoking abstinence has significant health benefits for the mother, as most new mothers will be young enough to minimise long-term harm, particularly from cancers and cardiovascular disease.^14^ Maternal smoking is the primary source of infant and child secondhand smoke exposure,^15 16^ a substantial cause of ill health and mortality.^17^ This has an intergenerational effect: children of smoking mothers are twice as likely to become smokers.^18^ The total NHS annual cost of smoking continuation, or returning to smoking following pregnancy, is estimated to range between £8.1 and £64 million annually for treating maternal health problems alone.^19^ While, in 2015/2016 the cost of admitted patient care in children attributable to passive smoking in England was an additional £5–12 million.^20^

Following our comprehensive intervention development work and patient and public involvement, it is clear that postpartum smoking relapse is a complex problem requiring a multifaceted solution. Our research team have developed a novel intervention combining behavioural, digital and relapse prevention support, ‘BabyBreathe’. The intervention is theory based and uses behaviour change techniques, each supported by available evidence.^21^ The development process involved working with pregnant and post-partum people, families and healthcare professionals to design an intervention that would fit in and work alongside usual care (universal health visiting service in the UK), be feasible to implement in practice and be acceptable.^12^

## Aims and objectives

### Aim

To assess the effectiveness and cost-effectiveness of the BabyBreathe intervention in comparison to usual care, for supporting long-term smoking abstinence for mothers who have recently given birth and have stopped smoking during pregnancy or during the 12 months prior to pregnancy.

### Objectives

To run an internal pilot study, with clear stop/go trial embedded criteria, primarily to test recruitment systems.To definitively test the effectiveness of BabyBreathe in comparison with usual care, by comparing smoking abstinence rates at 12 months postpartum between trial groups.To undertake a cost-effectiveness analysis of BabyBreathe in comparison with usual care based on healthcare resource use of mother and infant and maternal health-related quality of life (HRQoL).To undertake an embedded mixed-methods process evaluation to assess delivery, implementation, fidelity and contamination and to identify mechanisms of action by exploring which intervention components may be particularly effective, for which women, in which contexts.

## Methods and analysis

This protocol is reported in accordance with the Standard Protocol Items: Recommendations for Interventional Trials recommendations^22^ and the Template for Intervention Description and Replication (TiDIER) guidelines^23^ (see online supplemental file).

10.1136/bmjopen-2023-076458.supp1Supplementary data

### Trial design

BabyBreathe is a multicentre, two-arm, superiority, parallel group, individually randomised, controlled trial of a complex intervention to prevent return to tobacco smoking postpartum, with internal pilot, including economic evaluation and process evaluation.

### Study setting

The setting is ‘real world’ with the intervention integrated into, or offered as an adjunct to, standard antenatal and postnatal care. Trial recruitment hubs (Norfolk, London, North East of England, and Lothian, Scotland) have been selected to ensure a diverse sample, with an additional ‘remote’ recruitment hub to maximise recruitment rates (across the UK, including Wales and Northern Ireland).

### Patient and public involvement

Two abstinent postpartum women were involved in development of intervention materials, and are included as members of our trial steering group, to advise on study progress and dissemination.

### Population

We will seek pregnant people who have quit tobacco smoking in the 12 months before or during pregnancy, where smoking abstinence is defined as having stopped smoking for at least 4 weeks prior to recruitment.

#### Inclusion criteria

Pregnant people who have stopped smoking completely in the 12 months prior to pregnancy, or at any time during pregnancy.At 26 weeks gestation or any time following this up until birth, participant confirms having not smoked a single puff of a cigarette for at least 4 weeks.Able to read and understand English.Willing and able to give informed consent for participation in the study.Expired carbon monoxide (CO) reading less than four parts per million (ppm).^24^

#### Exclusion criteria

Under the age of 16.

### Recruitment and screening

Multiple recruitment strategies will be used to reach target sample size (n=880). Potential participants will be identified by hospital and community midwives, research midwives (Clinical Research Network,CRN) or sonographers, during routine antenatal appointments (eg, booking appointment, routine scan appointment for dating or fetal anomaly scan) or by screening medical records. Participants may also be identified by smoke-free services, health visitors or by self-referring (eg, via adverts in health or community settings, using targeted online recruitment or media adverts). Potential participants will be screened for eligibility by the midwife (or by other healthcare professionals, in other health settings), or by a study researcher for direct referrals. The screening process can take place at any time during pregnancy, though the target is to identify participants ahead of 26 weeks pregnancy.

Eligible participants will be provided a brief patient information leaflet, either directly or indirectly via an online link, explaining the study and permission will be requested to pass their contact details to the research team. A health professional or a research team member will enter their details into a study database (Research Electronic Data Capture (REDCap)^25^) that will automatically generate a short messaging service (SMS)/email to an electronic patient information sheet and e-consent form containing full reassurance of confidentiality. If participants are unable or unwilling to consent electronically, study researchers will contact potential participants by telephone to complete consent. Once consent is completed, participants will provide further details so they can be contacted from 26 weeks pregnancy with the link to the eligibility confirmation questionnaire.

Participants will be asked to confirm eligibility by replying via a link sent by text or email (according to preference), and will provide their address to enable postage of a CO monitor (iCO monitor, Bedfont) in order to confirm eligibility using an expired CO reading of less than 4 ppm (this is the standard cut-off used in pregnancy).^24^ Participants will be asked to download the study specific CO monitor application (iCOBabyBreathe) which will provide the REDCap database with two CO readings. The highest of the two readings will be recorded. Where CO readings ≥26 weeks gestation are able to take place in person as part of standard care, CO readings may be obtained by a member of the clinical team or a researcher to confirm participant eligibility.

Once the participant has given informed consent and eligibility is confirmed through a CO reading, a link will be automatically generated through text/email to the participant to complete the baseline questionnaire.

### Randomisation

Completion and submission of the baseline measures will trigger randomisation (see trial flow diagram, figure 1). Participants will be individually randomised in a 1:1 ratio to the control or intervention groups using a computerised web-based randomisation system managed and accessed only by Norwich Clinical Trials Unit, to ensure adequate sequence generation and allocation sequence concealment. The randomisation system will stratify by recruitment hub, partner smoking status (partner smoking and partner non-smoking/no partner) and time of quit (before or during pregnancy), as these factors are likely to predict relapse.

**Figure 1 F1:**
[figure not shown]
Trial flow diagram. CO, carbon monoxide; PIS, patient information sheet.

### Blinding

Blinding is not possible due to the nature of the trial and intervention. The primary outcome is objectively assessed using biochemically validated CO verified smoking abstinence. Therefore, we consider that there is low risk of bias for the primary outcome.

### Internal pilot

The Independent Data Monitoring and Ethics Committee and Independent Trial Steering Committee (TSC) will scrutinise recruitment and protocol fidelity at 6 months into recruitment to establish continuation or stopping the trial at the pilot stage.

### Trial allocation groups

#### Control

Control participants will receive usual antenatal and postnatal care as per the NHS maternity care pathway (ie, no routine relapse prevention support). Usual care varies across the UK and sites have been purposively selected to reflect the variations in routine care. Commonalities in usual care across all the sites include pregnant women being routinely screened for smoking status by their midwife at their first antenatal booking appointment. If a participant reports to be currently smoking, or has a CO reading of 4 ppm or more, they are automatically referred for stop smoking support via NHS commissioned stop smoking services (opt-out referral). Midwifery support focuses on abstinence in pregnancy and only includes brief advice about the opportunity to maintain abstinence postpartum and in the long-term. The usual care group will receive standard ante and postnatal care, as per mandated midwifery and health visitor contacts. These visits may be face-to-face appointments, or they may be remote video or telephone appointments due to the COVID-19 pandemic and local service provision protocols.

#### Intervention

Intervention participants will receive usual care plus the BabyBreathe package of support. The BabyBreathe intervention is informed by the Capability Opportunity Motivation-Behaviour model (COM-B) and Behaviour Change Wheel,^26^ with full consideration of post partum context-specific concerns. The intervention is a package of support designed to be delivered at low cost alongside usual care and existing healthcare services. All intervention components have been developed and initially tested in our preliminary work with pregnant and postpartum people and partners (MRC MR/PO16944/1).^12^ The intervention comprises three main stages:

##### Antenatal support up to birth

Usual care provision (as delivered in any given site area) will continue also to be provided to the intervention group.BabyBreathe relapse prevention leaflet.Partner/friend/relative relapse prevention leaflet—content has been designed to encourage partners/friends/relatives to support the participant to stay smoke free after delivery, and to promote active cessation for partners/friends/relatives themselves, where needed.Brief advice from a health visitor, health visiting team member or member of the research team trained to deliver the intervention (in-person, or remote). This advice is standardised and scripted following a protocol, with tailored options including positive praise for achieving smoking abstinence and brief advice about the importance of staying smoke-free. Active signposting to the BabyBreathe digital/remote elements are included in this discussion.Electronic CO testing—participants are given an iCO monitor (Bedfont) for individual use. Those in the intervention group will be encouraged to use the iCO monitor to self-monitor CO levels at any time during the study (control participants are only prompted to submit a research reading at baseline and study end).BabyBreathe website and app—these resources have been specifically developed and the app operates on both Android and iOS (iPhone) operating systems. The website and app can be accessed using a unique code. Users may input details such as the date they quit smoking, their estimated delivery date and may access self-help support, health information and advice, including innovative motivational tools, such as a health calendar and a closed online social support group, in preparation for entering the immediate postpartum period.At each subsequent health visitor contact (in-person, or remote), support for maintaining smoking abstinence will be briefly reiterated alongside usual care, where possible.

##### Immediate postnatal period

BabyBreathe box—once the site team is alerted about the birth and input these data into the REDCap database, the central trial team will post out a BabyBreathe box. This is a physical box, designed to fit through a letter-box. The box includes self-incentive tools (eg, reward chart, journal, photograph frame), free preventative Nicotine Replacement Therapy (NRT, Nicorette Icy White 2 mg, 30 pieces), plus advice and support to use NRT or e-cigarettes for relapse prevention.SMS or app notification tailored support—This will be triggered by the birth notification, delivering a programme of tailored relapse prevention messages. Messages start daily, with a diminishing schedule over 12 months. At regular intervals participants are asked to confirm smoking status, and either then stay on the ‘smokefree’ or ‘lapse’ track of tailored messages. There is the option to opt out by texting ‘stop’ at any time.

##### Postnatal period and beyond

At home/virtual postnatal visit with a health visitor, associated practitioner or BabyBreathe intervention trained researcher at around 10–14 days postpartum, when care is handed over from midwives to health visitors. At this visit, the health visitor will discuss smoking status, give positive praise, offer relapse prevention support, affirm that the BabyBreathe box has been received and discuss contents of the BabyBreathe box, and text/app message use.Reiteration of support from health visitors or associated practitioners, up to 12 months postpartum—all subsequent postpartum routine health visitor appointments for the duration of the study will be undertaken by the same health visitor or health visiting team member where possible, to assure continuity of care, which would be anticipated as part of usual practice. Positive praise will be offered for sustained smoking abstinence and the importance of relapse prevention will be emphasised. Participants will be encouraged to continue to engage, or to re-engage, with the full suite of BabyBreathe resources. Cessation support (referral) will be offered to partners where necessary and appropriate. For those who relapse, referral for cessation support will also be offered.

See figure 2, for examples, of the components of the BabyBreathe intervention.

**Figure 2 F2:**
[figure not shown]
Examples of BabyBreathe intervention components.

### Outcomes

See table 1 for participant timeline of interventions and assessments.

**Table 1 T1:** BabyBreathe participant timeline schedule of enrolment, interventions and assessments

Antenatal				Postnatal				
**Screening** (**from 8 weeks to birth)^*^**	**Confirm eligibility (from 26 weeks**)	**Baseline (from confirmation of eligibility**)	**Health visit (from randomisation up to birth)**	**Postnatal within 7 days**	**Health visit (10–14 days post partum**)	**Health visits (all subsequent routine**)	**6-month follow-up**	**12-month follow-up**
X								
X								
X								
	X							X
		X						
		X					X	X
		X					X	X
		X					X	X
		X					X	X
		X					X	X
		X					X	X
		X					X	X
		X					X	X
		X					X	X
		X					X	X
		X						
			X	X	X	X	X	X
				X				
								X
								X

*Potential participants will be variously identified during pregnancy: identified at pregnancy booking visit, at dating scans at (8–12 weeks) and/or 20-week scan, by screening records, or at routine care pregnancy appointments occurring anytime between start of pregnancy and 26 weeks of pregnancy, and by self-referral through responding to adverts. These practices will vary and due to pandemic-related restrictions of appointments that may happen remotely. Those missed can be eligible for recruitment following 26 weeks of pregnancy, until the end of pregnancy.

#### Primary outcome

The primary effectiveness outcome is self-reported continuous smoking abstinence, from birth, biochemically validated by CO monitoring at 12 months postpartum, with cut-off of less than 8 ppm (ie, a reading of 7 ppm or less) for those who are not pregnant, or with a cut-off of less than 4 ppm if they are pregnant at this time point, according to the Russell standard.^27^ Adapting the Russell standard for the postpartum population, we will grant a period of ‘grace’, allowing up to five smoking lapses (a one off instance of smoking) between the birth of the baby and the 12-month follow-up, before the outcome is counted as relapse. Participants will provide CO readings electronically, using the iCO monitor (Bedfont) and study app (iCOBabyBreathe) provided at baseline. Participants will provide the REDCap database with two CO readings at entry and follow-up. The highest of the readings will be recorded. Where CO readings take place in person as part of standard care, or research visits, or when participants request help with taking a CO reading, these readings may be used.

#### Secondary outcomes

Secondary outcomes (table 1) measured at 6 and 12 months post partum by online self-report, or researcher follow-up, include self-reported point prevalence abstinence, self-reported time to relapse, participant-reported partner smoking status, self-efficacy (single item, self-report), Edinburgh Postnatal Depression Scale,^27^ behavioural support use (eg, support from a stop smoking service), nicotine product use, perceived stress,^28^ the Alcohol Use Disorders Test for Consumption (AUDIT-C),^29^ health related quality of life (HRQoL) using the EQ-5D-5L.^30^ Infant health outcomes (eg, minor infections requiring General Practitioner (GP) visits and more serious ill health requiring hospitalisation), participant and infant health resource use and cost-effectiveness will be measured at 12 months postpartum using a combination of GP patient records and participant self-report.

### Sample size

If the primary outcome (continued smoking abstinence) occurs in 25% of the control group (based on an estimated relapse rate of 75%^13^) compared with 35% of the intervention group, then we estimate that we will need 880 participants (440 per group) to have 90% power to detect this 10% between group difference at the 5% level of significance. We estimate this difference between control and intervention groups is realistic based on recent trials.^31^ Loss to follow-up or withdrawal is not considered within the sample size calculation, as all those lost to follow-up will be counted as returned to smoking, as is the usual convention in smoking cessation trials.^32^

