### Data analysis

We will use descriptive statistics to present the baseline characteristics of the two study groups. We will use χ^2^ tests to compare follow-up rates between the study groups, to establish whether there is differential drop out. Analysis of smoking status will be based on the intention-to-treat principle by analysing individuals according to the treatment they were allocated to regardless of compliance. Individuals for whom we do not have the primary outcome data will be assumed to have returned to smoking. Analysis of the primary outcome will be based on a logistic regression model, adjusting for the stratification variables used in the randomisation algorithm. Secondary analysis will adjust for factors known to be predictive of relapse which will be agreed with the TSC and added to the statistical analysis plan (SAP) prior to analysis. Secondary outcomes will be analysed in a similar fashion using a general linear model. Missing data patterns will be examined, and if appropriate, multiple imputation will be undertaken. The SAP is preregistered (on the Open Science Framework (OSF))—see online supplemental appendix 1. The analysis plan may include analysis suggested by the qualitative analysis, such as subgroup analysis or mediation analysis. Any analysis will be prespecified before data lock and published in the SAP prior to any data analysis.

10.1136/bmjopen-2023-076458.supp2Supplementary data

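### Counting the missing as smokers does not by itself justify leaving loss out of the sample size: the 90% power holds only if 25% and 35% are already rates after that rule, which the protocol does not say

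*Protocol article*

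**What the plan says.** The Sample size section of the protocol article assumes that the primary outcome "occurs in 25% of the control group (based on an estimated relapse rate of 75" per cent), "compared with 35% of the intervention group". From this it concludes that "we will need 880 participants (440 per group") are required "to have 90% power to detect this 10% between group difference" "at the 5% level of significance".

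On attrition, the same section says: "Loss to follow-up or withdrawal is not considered within the sample size calculation, as all those lost to follow-up will be counted as" having gone back to smoking. It calls this the usual convention in cessation trials.

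The Data analysis section applies the same rule to the primary analysis: "Individuals for whom we do not have the primary outcome data will be assumed to have returned to smoking".

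Under Primary outcome, success needs both self-reported continuous abstinence from birth (with up to five lapses allowed) and a CO reading below the cut-off at 12 months.

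The article gives no expected loss rate. It does not say whether the 75% relapse figure, or the trials behind the 10-point difference, already count people lost to follow-up as smokers.

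**The concern.** The article gives one reason for leaving loss out: the lost will be scored as smokers. That rule protects the number analysed. It does not protect the effect size. A participant who is truly abstinent at 12 months but supplies no CO reading, or cannot be reached, moves from success to failure. If this happens at the same rate in both arms, both success rates shrink in proportion, and so does the difference between them.

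This can happen under the trial's own procedures. The reading is normally taken remotely with a monitor and app issued at baseline, more than a year before the 12-month follow-up. The Retention section provides for researchers to contact non-responders and collect self-report where possible, but self-report alone does not meet the primary outcome.

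At stake is the design claim of 90% power for a 10-point difference. Anyone judging whether a null result had a fair chance of being positive will rely on it.

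**Working it through.** **Inputs from the protocol article**
- Control rate p₁ = 0.25, intervention rate p₂ = 0.35, power 90%, significance level 5%, 440 per arm (Sample size).
- Allocation 1:1 (Randomisation).
- Missing primary outcome counted as smoking (Data analysis).

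**Assumed, because the article gives no figure**
- L = share of true abstainers without 12-month outcome data, equal in both arms, over a range of 5% to 30%.

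**Step 1. Reproduce the stated size.** With pooled variance under the null, two-sided, no continuity correction and p̄ = (p₁ + p₂)/2:

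n per arm = [1.960·√(2p̄(1−p̄)) + 1.2816·√(p₁(1−p₁) + p₂(1−p₂))]² / (p₂ − p₁)²

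- p̄ = 0.30, so √(2 × 0.30 × 0.70) = 0.6481.
- √(0.25 × 0.75 + 0.35 × 0.65) = 0.6442.
- n = (1.2702 + 0.8256)² / 0.01 = 439.2, rounded up to 440 per arm, or 880 in total.

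This matches exactly, and power at 440 per arm is 90.0%. The article does not say whether the 5% is one- or two-sided. A one-sided test would give 716, so two-sided is what was used.

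**Step 2. Apply the missing-as-smoking rule to rates that hold before it.** Relapsers are failures whether or not they are followed up, so only missing abstainers change category:

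p₁′ = 0.25(1 − L), p₂′ = 0.35(1 − L), difference = 0.10(1 − L)

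Power = Φ{[(p₂′ − p₁′)·√440 − 1.960·√(2p̄′(1−p̄′))] / √(p₁′(1−p₁′) + p₂′(1−p₂′))}

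Worked at L = 20%: rates 0.20 and 0.28, p̄′ = 0.24. The numerator is 0.08 × 20.976 − 1.960 × 0.6040 = 0.4943, the denominator is 0.6013, the ratio is 0.822, and Φ(0.822) = 0.794.

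| L (assumed) | Control | Intervention | Difference (points) | Power, 440 per arm |
|---|---|---|---|---|
| 0% | 25.0% | 35.0% | 10.0 | 90.0% |
| 5% | 23.75% | 33.25% | 9.5 | 87.9% |
| 10% | 22.5% | 31.5% | 9.0 | 85.4% |
| 20% | 20.0% | 28.0% | 8.0 | 79.4% |
| 30% | 17.5% | 24.5% | 7.0 | 72.3% |

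**Step 3. The other reading.** If 25% and 35% are rates after the rule, power stays at 90.0%. The underlying abstinence rates must then be higher: 0.25/(1 − L) and 0.35/(1 − L). At L = 20% these are 31.25% and 43.75%, a 12.5-point difference. They are also the rates among those followed up if relapsers go missing at the same 20%.

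**Step 4. Unequal shares between arms.** With 20% of abstainers missing in control and 10% in intervention, the rates are 20.0% versus 31.5% and power is 97.5%. With 10% and 20%, they are 22.5% versus 28.0% and power is 46.7%.

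**The case against.** The strongest defence is that nothing is miscalculated and that the text can be read so that nothing is wrong. The Sample size section speaks of how often the primary outcome occurs in each group, and the Data analysis section scores that outcome with missing counted as smoking. Taken together, 25% and 35% could be planning rates for the outcome as scored, over all 440 per arm. Those lost are then already among the failures, and 90% is right. If the source trials followed the same convention, a 75% relapse rate taken from them would already include the lost. Those sources are not at hand, so this cannot be ruled out.

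Two further points stand:
- L is loss among abstainers, not overall loss. If, say, 5% of abstainers and 25% of relapsers were missing, overall loss in control would be 0.25 × 5% + 0.75 × 25% = 20%, yet the rates would shrink by only 5% and power would be about 88%. If everyone lost had truly relapsed, nothing would shrink.
- The design works to limit loss, with a reminder, up to five researcher contacts, several modes of data collection, a voucher, and in-person or assisted CO readings.

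What the defence does not rescue is the reason as written. The article justifies ignoring loss by the scoring rule alone. It does not say that the planning rates were set with that rule applied.

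**Conclusion.** The point holds in a conditional form. The rationale for leaving out loss is invalid as stated, because the rule secures the denominator and not the 10-point difference. The 90% power holds only if 25% and 35% are rates after missing is counted as smoking, and the article leaves this open. If they are rates before the rule, power with 880 is about 88%, 85%, 79% and 72% when 5%, 10%, 20% and 30% of true abstainers lack outcome data. Those figures rest on assumed shares that are equal in both arms; unequal shares can move power either way.

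A reader might go further and infer that 880 is an arithmetic error, or that the trial is underpowered. The document supports neither. The 880 follows exactly from the stated inputs, no loss rate is given, and the reading that preserves 90% remains open. This is a justification to be corrected and an input to be defined, not a demonstrated shortfall.

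**What to change.** Keep N at 880 and replace the sentence that sets loss aside. State which kind of rate 25% and 35% are:

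- **If after missing-counted-as-smoking:** say so, and give the implied rates among those followed up under a stated assumption, for example about 31% versus 44% if 20% of participants in both arms lack data regardless of smoking status.
- **If before that rule:** restate the power of 880 as conditional on the share of true abstainers without 12-month outcome data, assumed equal in both arms: about 88% at 5%, 85% at 10%, 79% at 20% and 72% at 30%.

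In either case, note that the shares are assumptions, that they describe loss among abstainers and not overall loss, and that unequal loss between arms can raise or lower power.

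The cost is a few sentences, with no change to recruitment, conduct or the primary analysis. The downside for the sponsor is that the stated power may become less favourable, or the effect assumed among those followed up may be seen to exceed 10 points.
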